### Randomisation

Randomisation is stratified by centre and disease severity (FEV_1_ < 50 % vs. FEV_1_ ≥ 50 %) to preserve homogeneity between arms with regard to severity of clinical status. Randomisation is web-based and performed via the WebCRF program developed by the Unit for Applied Clinical Research at the Norwegian University of Science and Technology in Trondheim. The tool uses a computerised block randomisation, and the size of the first, smallest and largest blocks is established based on the total number of patients expected to be included in the study. The randomisation sequence generated is concealed from the study team by the program. The same WebCRF program is used to fill out electronic case report forms (CRFs). This allows patient data from several centres to be entered into the same database.

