### Recruitment and study procedures

At enrolment, a clinical assessment is performed for all the patients by appropriately trained study personnel blinded to group allocation. Participants are asked to perform spirometry, the 6-min walking test [36] and complete the study questionnaires (Table 1). Participants are also provided brochures containing information about PR, physical activity and training, diet, self-management, motivation and lifestyle changes, smoking cessation and oxygen therapy.

**Table 1 Tab1:** Data collected at baseline and follow-up visits

Data collected	Baseline	6-month	1-year	2-year
Clinical history and patient’s characteristics	X			
Pharmacological treatment	X			
Spirometry	X	X	X	X
6-min walking test	X	X	X	X
MMRC Dyspnoea Scale	X	X	X	X
COPD Assessment Test	X	X	X	X
EQ-5D Health Questionnaire	X	X	X	X
Generalised Self-Efficacy Scale	X	X	X	X
Hospital Anxiety and Depression Scale	X	X	X	X
Level of physical activity	X	X	X	X
Healthcare utilisation		X	X	X
Patient Global Impression of Change		X		

After enrolment, patients in the telerehabilitation and the treadmill arms undergo a supervised session on the treadmill with an experienced research physiotherapist to learn how to safely exercise at home, receive information on how to make progress in the programme and are given the opportunity to clarify any questions related to equipment management. Patients in the telerehabilitation arm also receive training on the use of the study website. A test videoconferencing session is also performed by the local research team to guarantee proper equipment functioning. Patients can always contact the research team in case of technical issues.

At 6-month, 1-year and 2-year, patients undergo a clinical reassessment and are asked to complete the study questionnaires (Table 1). During data collection patients are encouraged to continue participating in the study. Patients are discharged from the trial after 2 years, those in the telerehabilitation and the treadmill arms can keep the equipment at the end of the study.

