A cost-utility analysis will be performed to verify whether the telerehabilitation and the treadmill interventions are cost-effective. The perspective of the healthcare authority will be adopted with respect to costs. The following cost components will be included in the analysis: a) hospital resources, b) delivery of the telerehabilitation intervention, and c) equipment. Hospital resources will include hospitalisations, ED presentations, outpatient visits, and rehabilitation. Unit cost for each resource will be based on the specific public tariffs from the national DRG system. Delivery of the telerehabilitation intervention will include the time used by the project team to install the equipment in the patient’s home and provide training, and the time used by the physiotherapist to supervise the patients. Equipment costs for the telerehabilitation arm and the intervention arm will be calculated based on a 5-year amortisation period. All costs will be expressed in Euros (€). Utility will be measured in terms of quality adjusted life years (QALYs), based on the answers of the EQ-5D questionnaires at baseline, 6 month, 1–2 years. Utility values will be calculated using the European EQ-net VAS set, and only if all the five dimensions are answered. The incremental cost-effectiveness ratio will be computed as differential costs and differential QALYs.

Patients’ perspectives in participating in long-term telerehabilitation will be explored through qualitative interviews with semi-structured questions. Interviews will be conducted before telerehabilitation, after 1 year and after 2 years, with 5–8 patients in the telerehabilitation arm at each site. Interviews will be recorded on audio digital file, transcribed verbatim and analysed via Nvivo 10.0 upon the theoretical frame of the learning theory [43].

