### Statistical analysis

Descriptive statistics at baseline will be reported as means ± SD for normally distributed continuous variables, or medians with 25–75th percentiles in the case of skewed distribution. Normality of distribution will be tested by means of the nonparametric Kolmogorov-Smirnov test. An intention-to-treat analysis will be performed on all randomised subjects to provide unbiased comparisons among groups and avoid the effects of dropout. The primary outcome and related secondary outcomes will be measured through the Incidence Density, defined as the number of events in a group divided by the total person-time accumulated during the study in that group [44]. Differences between study arms will be tested by the Comparison of Incidence Rates. A two-sided test and a significance level of *α* = 0.05 will be used. All events from the day after randomisation to patient exit/death will be included. Other secondary outcomes will be measured as changes from baseline to all assessment time points. Changes of the secondary outcomes will be tested by use of linear mixed models, which allow accounting for repeated measures collected in a longitudinal design. Moreover, linear mixed models deal better with dropouts that other methods used for repeated measures, and use of imputation techniques for missing data is not necessary. A *p*-value <0.05 will be considered significant for all tests. All statistical analyses will be performed by using IBM SPSS Statistics.

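### The cost-utility section defines incremental QALYs without adjustment for baseline EQ-5D; adjusting would give a more precise estimate at almost no cost

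*Protocol article*

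**What the plan says.** All references are to the protocol article.

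- **Outcome measures, cost-utility paragraph.** QALYs are "based on the answers of the EQ-5D questionnaires at baseline, 6 month, 1–2 years". On valuation: "Utility values will be calculated using the European EQ-net VAS set, and only if all the five dimensions are answered". The contrast is given as: "The incremental cost-effectiveness ratio will be computed as differential costs and differential QALYs". Baseline adjustment is neither stated nor ruled out.
- **Statistical analysis.** "Other secondary outcomes will be measured as changes from baseline to all assessment time points", tested with linear mixed models. Table 2 lists cost-effectiveness as a secondary outcome with its own measure, cost per QALY. Nothing says that the mixed model extends to QALYs or the ICER.
- **Recruitment and study procedures, Table 1.** The row "EQ-5D Health Questionnaire" is marked at baseline and at all three follow-up visits. On timing: "At enrolment, a clinical assessment is performed for all the patients by appropriately trained study personnel blinded to group allocation". This implies that the baseline score precedes randomisation, though the article does not say so outright.
- **Randomisation.** "Randomisation is stratified by centre and disease severity", the severity factor being FEV1 below 50% versus 50% or above. Baseline utility is not a stratification factor.
- **Sample size.** 40 patients per arm, followed for 2 years.

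**The concern.** A 2-year QALY is a level accumulated over time, so a patient who starts with a higher utility tends to finish with more QALYs whatever the treatment. Describing the questionnaire outcomes as changes from baseline does not deal with this, because a QALY total has no baseline value of its own to subtract. If arms of 40 happen to differ in baseline EQ-5D, part of that difference appears in the realised QALY contrast.

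The Abstract and the Discussion both say that the trial will show whether long-term telerehabilitation is cost-effective. The QALY contrast is the denominator of the ratio meant to show this. A ratio with a small denominator reacts strongly to modest movements in it, so avoidable noise there is worth removing. Fixing the estimator in advance also avoids a choice between adjusted and unadjusted ICERs once results are known.

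**Working it through.** **The plan's own figures.** The article states no QALY or ICER figure, so there is none to reproduce. Its one computed design figure concerns the primary outcome: (1.960 + 1.645)² × (2.0 + 1.2) / (2.0 − 1.2)² = 64.97, which agrees with the stated 65 person-years per group. It has no bearing on this point.

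**Inputs from the article.** Visits at 0, 0.5, 1 and 2 years; n = 40 per arm.

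**Assumed inputs.** Utility SD s = 0.20 (range 0.15 to 0.25), equal correlation r between any two visits of 0.4 to 0.7, QALYs by the trapezoid rule, complete follow-up.

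**Step 1, weights.** The trapezoid rule gives 0.25, 0.50, 0.75 and 0.50, which sum to 2.0. Baseline carries 0.25/2.0 = 12.5% of the weight.

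**Step 2, chance imbalance at baseline.** SE of the difference = s√(2/40) = 0.034, 0.045 and 0.056 for s = 0.15, 0.20 and 0.25.

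**Step 3, carry-over to QALYs.** Slope of QALY on baseline utility = 0.25 + 1.75r. Shift for a one-SE imbalance = slope × SE.

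**Step 4, variance.** The squared weights sum to 1.125, so Var(QALY) = s²[1.125 + (4 − 1.125)r] = s²[1.125 + 2.875r]. Share explained by baseline: R² = (0.25 + 1.75r)² / (1.125 + 2.875r). SE of incremental QALYs = √(2 Var/40) unadjusted, multiplied by √(1 − R²) when adjusted.

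Results at s = 0.20:

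| r | slope | shift per 1 SE | R² | SE unadjusted | SE adjusted |
|---|---|---|---|---|---|
| 0.4 | 0.950 | 0.042 | 40% | 0.067 | 0.052 |
| 0.5 | 1.125 | 0.050 | 49% | 0.072 | 0.051 |
| 0.6 | 1.300 | 0.058 | 59% | 0.076 | 0.048 |
| 0.7 | 1.475 | 0.066 | 69% | 0.079 | 0.044 |

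Over the full assumed range, the shift per one SE runs from 0.032 (s = 0.15, r = 0.4) to 0.082 (s = 0.25, r = 0.7). At r = 0.5 the gain in precision equals multiplying the sample size by 1/(1 − 0.494) = 1.98.

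**Step 5, where the shift comes from.** At s = 0.20 and r = 0.5, the baseline term contributes 0.25 × 0.0447 = 0.011. Correlation with later scores contributes 1.75 × 0.5 × 0.0447 = 0.039. The total is 0.050, of which the baseline term is about a fifth.

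**Step 6, what remains after adjustment.** The chance that the estimate misses the truth by more than 0.05 QALY in either direction is 2[1 − Φ(0.05/SE)]. At s = 0.20 and r = 0.4, 0.5 and 0.7 this is about 46%, 49% and 53% unadjusted, and about 34%, 33% and 25% adjusted.

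**Step 7, dropout.** If 20% had no usable QALY, n = 32 per arm and every SE rises by √(40/32) = 1.118. At r = 0.5 that gives 0.080 unadjusted and 0.057 adjusted. The proportional gain is unchanged.

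**The case against.** The strongest reply is that the sentence on the ICER is merely its general definition, and a baseline-adjusted ICER also fits it. On this view the article is silent on adjustment, and a condensed article may leave that to an analysis plan or health-economic plan that is not shown. This stands in part. A reader might infer that the plan commits to a raw difference, and the text does not support that. The point survives because the section does state the contrast, alongside the value set, cost components and amortisation period. Followed as written, it yields a noisier estimate than one available from data already scheduled.

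Two further stronger readings are tempting and should be resisted:

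- **That baseline imbalance biases the QALY comparison, or is systematically credited to treatment.** Under randomisation the unadjusted difference is unbiased. What suffers is its precision and the realised estimate in a given trial.
- **That the fault lies in including a pre-randomisation score in the QALY.** Step 5 shows that this term accounts for little of the shift. The rest is the ordinary effect of an unadjusted prognostic covariate. Dropping baseline from the QALY would not cure it, and including it is not an error.

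It is also fair to object that the sizes rest on assumptions. The article gives no SD, correlation or expected QALY gain, so it cannot be shown from the document that the cost-effectiveness conclusion would change. Step 6 confirms that 40 per arm leaves substantial chance error even with adjustment.

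**Conclusion.** The point holds as one of precision and prespecification for a secondary outcome. The stated contrast names no adjustment for baseline EQ-5D, and the change-from-baseline mixed model is not said to cover QALYs.

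Assuming SD 0.20, correlation 0.4 to 0.7, trapezoid QALYs and complete follow-up, a one-SE baseline imbalance moves incremental QALYs by about 0.04 to 0.07. Adjustment removes about 40% to 69% of the variance. The direction of the gain needs only that later utility correlates with baseline; its size depends on the assumed values. Adjustment reduces chance error without removing it. The change is worth making, but the primary analysis does not depend on it.

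**What to change.** In the cost-utility paragraph of Outcome measures, state that incremental QALYs for each contrast are the arm coefficient from a patient-level regression of 2-year QALYs on arm, baseline EQ-5D utility, centre and FEV1 stratum. State that this coefficient is the ICER denominator and that the unadjusted ICER is reported as a sensitivity analysis. If an unseen analysis plan already says this, a cross-reference is enough.

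The cost is a sentence or two and one regression; no new data are needed. The small downside is that a missing or incomplete baseline EQ-5D must be handled, for example by imputing the overall baseline mean. The rule should be stated with the model.

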### Adverse events and dropouts

Adverse events, including deaths, treadmill injuries and other unspecified reasons, will be recorded in the WebCRF program. Technical problems will be recorded by each participating centre into a separate database. Dropouts will occur if patients notify the research team that they do not want to participate any longer to the study and therefore withdraw their consent. In this case the project team might collect the equipment upon request. Patients who do not participate actively in the intervention will still be included in the study, and analysed according to the intention-to-treat approach. They will keep the project equipment as long as they want.

### Statistical analysis

Descriptive statistics at baseline will be reported as means ± SD for normally distributed continuous variables, or medians with 25–75th percentiles in the case of skewed distribution. Normality of distribution will be tested by means of the nonparametric Kolmogorov-Smirnov test. An intention-to-treat analysis will be performed on all randomised subjects to provide unbiased comparisons among groups and avoid the effects of dropout. The primary outcome and related secondary outcomes will be measured through the Incidence Density, defined as the number of events in a group divided by the total person-time accumulated during the study in that group [44]. Differences between study arms will be tested by the Comparison of Incidence Rates. A two-sided test and a significance level of *α* = 0.05 will be used. All events from the day after randomisation to patient exit/death will be included. Other secondary outcomes will be measured as changes from baseline to all assessment time points. Changes of the secondary outcomes will be tested by use of linear mixed models, which allow accounting for repeated measures collected in a longitudinal design. Moreover, linear mixed models deal better with dropouts that other methods used for repeated measures, and use of imputation techniques for missing data is not necessary. A *p*-value <0.05 will be considered significant for all tests. All statistical analyses will be performed by using IBM SPSS Statistics.

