## Background

Chronic obstructive pulmonary disease (COPD) is characterised by a persistent airflow limitation that is usually progressive [1]. Patients experience frequent acute exacerbations, characterised by worsening of respiratory symptoms [2] which may lead, in the worst cases, to a hospital admission [3]. COPD poses a substantial burden on healthcare budgets. The largest part of the health service expenditure is for hospitalisations and emergency department (ED) presentations, which commonly occur in the latter stages of the disease [4]. Moreover, prior hospitalisations represent a risk factor for rehospitalisation in patients discharged after a severe exacerbation [5]. Hospital admissions for exacerbations do not only represent a burden for the healthcare system, but have also a negative impact on patients, who experience reduced physical activity, decreased exercise performance [6], and impaired quality of life, even in mild stages of the disease [7]. Dyspnoea, the most commonly reported symptom during acute events, is associated with anxiety and depression [8]. Importantly, reduced physical activity is the strongest predictor of mortality in patients with COPD [9].

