### Outcome measures

The primary outcome is the combined number of hospitalisations and ED presentations. Differences in the rate of events between the study arms will be measured at all assessment time points (Table 2). Data on hospitalisations and ED presentations, together with outpatient visits, will be collected from hospitals records (in Australia), regional systems (in Denmark) and national registries (in Norway). Details will include institution, date of admission, date of discharge, diagnosis-related group (DRG), diagnoses, procedures and associated cost. In addition, use of hospital resources will be recorded during the follow-up visits. Hospitalisations and ED presentations will be also analysed separately as secondary outcomes. Mortality will be monitored along the study together with dropouts.

**Table 2 Tab2:** Primary and secondary outcomes and related measures

Outcome	Measure
Primary outcome	
• Combined number of hospitalisations and ED presentations	• Incidence Density
Secondary outcomes	
• Hospitalisations • ED presentations • Mortality • Time free from first event • Health status • Quality of life • Anxiety and depression • Self-efficacy • Subjective impression of overall change • Physical performance • Level of physical activity	• Incidence Density • Incidence Density • Mortality rate • Days to first hospitalisation or ED presentation • COPD Assessment Test • EQ-5D • Hospital Anxiety and Depression Scale (HAD) • Generalised Self-Efficacy Scale (GSES) • Patient global impression of change scale (PGIC) • 6-min walking distance (6MWD) • Daily number of steps, minutes of moderate to vigorous physical activity and sedentary time during 1-week
• Cost-effectiveness • Experiences in telerehabilitation	• Cost-utility analysis (cost-per-QALY) • Qualitative interviews with semi-structured questions

Health status will be measured with the COPD Assessment Test (CAT) [37]. Health-related quality of life will be measured with the EQ-5D questionnaire [38]. Levels of anxiety and depression will be measured with the Hospital Anxiety and Depression Scale (HAD) [39]. Self-efficacy will be measured with the Generalised Self-Efficacy Scale (GSES) [40]. Subjective impression of overall change will be measured with the Patient global impression of change scale (PGIC) [41]. The study questionnaires, available in English, Norwegian and Danish with validated versions, will be collected along the study at different time points (Table 1).

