## Discussion

This study protocol described the methods used in this first RCT investigating the effects of long-term telerehabilitation in COPD. Patients with COPD often experience repeated exacerbations which lead to a worsening of their health condition and to hospital admissions [3]. Moreover, hospital readmissions are more likely to occur in patients with prior history of hospitalisations [5]. There is an increasing need for cost-effective treatment strategies for patients with COPD [22]. PR is a low-cost, integral component of COPD management [12]. PR is traditionally centre-based and offered either as a 6–12-week outpatient programme or as a 4-week inpatient programme. Available resources for PR are often limited, and patients living in rural areas especially suffer from poor availability of PR programmes [49]. Maintenance strategies are needed to sustain the benefits of PR over the long term [15]. However, these are scarcely documented, and the optimal combination of maintenance interventions after completion of a PR programme remains unknown [12]. Long-term telerehabilitation is an innovative intervention which might reduce hospital readmissions in COPD and thus limit healthcare utilisation. The results of this study will provide evidence on whether long-term telerehabilitation represents a cost-effective strategy for the follow-up of patients with COPD. The delivery of telerehabilitation services will also broaden the availability of PR and maintenance strategies, especially to those living in remote areas and with no access to centre-based exercise programmes.

Significant improvements in outcomes can be obtained with both supervised and unsupervised home exercise [50]. However, sustaining long-term exercise is generally difficult [17] for many reasons, including professional support, regular supervision [16], emotional safety, and maintenance of motivation [32]. We expect that standard care and unsupervised home exercise will be less beneficial than a telerehabilitation intervention where patients are supervised regularly by a physiotherapist via videoconferencing. The study was designed as a three-armed RCT to isolate the effects of placing training equipment in the patient’s home from those of telemonitoring.

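### The primary test and the sample size both treat repeat events in one patient as independent, so the nominal 5 % test is anti-conservative if patients' event rates differ

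*Protocol article*

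**What the plan says.** All of this is in the protocol article.

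- **Outcome (Outcome measures):** "The primary outcome is the combined number of hospitalisations and ED presentations". The two components are also analysed separately, with the same measure (Table 2).
- **Estimator (Statistical analysis):** incidence density is "the number of events in a group divided by the total person-time accumulated during the study in that group".
- **Events counted (same section):** "All events from the day after randomisation to patient exit/death will be included". Repeat events in one patient therefore all enter the numerator.
- **Test (same section):** "Differences between study arms will be tested by the Comparison of Incidence Rates", two-sided at 0.05. No dispersion parameter, patient effect, robust variance or patient-level count model is named. The same section does specify linear mixed models, chosen because they handle repeated measures, for the other secondary outcomes.
- **Sample size:** a null rate of 2 events per person-year, a rate ratio of 0.60 and 95 % power give 65 person-years per group. Forty patients per arm are enrolled, allowing for up to 20 % uniform dropout over 2 years.
- **Dependence between events:** the Background says that "prior hospitalisations represent a risk factor for rehospitalisation in patients discharged after a severe exacerbation", and the Discussion that "hospital readmissions are more likely to occur in patients with prior history of hospitalisations". The eligibility criteria admit moderate to very severe airflow limitation.

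**The concern.** A comparison of two pooled rates with Poisson variance is valid if all events in an arm arise independently at one common rate. A control patient is expected to have about 4 events in 2 years (2 per year × 2 years). If some patients are persistently more prone to admission than others, their repeat events carry less information than the same number of events spread over different patients. The test does not see this: its standard error depends only on total events and total person-time.

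With 40 patients per arm, a few frequent attenders could move an arm's rate appreciably. The consequence would be p-values that are too small and confidence intervals that are too narrow for the primary outcome, and likewise for hospitalisations and ED presentations taken separately. A chance difference between arms, in either direction, would be declared significant more often than the stated 5 %.

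**Working it through.** **1. Reproduce the plan's figure.** From the Sample size section: λ0 = 2.0, λ1 = 0.60 × 2.0 = 1.2, two-sided α = 0.05, power 95 %. The Poisson formula for two rates is

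T = (z₀.₉₇₅ + z₀.₉₅)² × (λ0 + λ1) / (λ0 − λ1)² = 12.995 × 3.2 / 0.64 = 64.97.

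This rounds to the stated 65 person-years. Two other Poisson variants give 66.4 (log rate ratio) and 63.9 (square root). One-sided versions give about 53 to 55 and do not fit. The stated figure contains no extra-Poisson variance.

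**2. Follow-up per patient.** With 20 % uniform dropout over 2 years, each arm yields 40 × (0.8 × 2 + 0.2 × 1) = 72 person-years. That is 1.8 years per patient and 2 × 1.8 = 3.6 expected events per patient under no effect. The 72 person-years exceed 65, so the dropout allowance is not the problem.

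**3. True error of the planned test.** Assume patient rates follow a gamma distribution with dispersion k, so that their SD is √k times the mean. A patient's count with mean μ then has variance μ(1 + kμ). The Poisson test understates the variance by the factor V = 1 + 3.6k, and its true two-sided error is 2 × [1 − Φ(1.96 / √V)]. The value of k is an assumption, because the article gives none.

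| k | V | Error, formula | Error, simulated |
|---|---|---|---|
| 0 | 1.00 | 5.0 % | 5.0 % |
| 0.05 | 1.18 | 7.1 % | not run |
| 0.1 | 1.36 | 9.3 % | 10.0 % |
| 0.25 | 1.90 | 15.5 % | 15.7 % |
| 0.5 | 2.80 | 24.1 % | 25.0 % |
| 1 | 4.60 | 36.1 % | 36.8 % |

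The simulation used 20,000 trials per row, with 40 patients per arm, a pairwise comparison and dropout as planned. It runs slightly above the formula because follow-up varies between patients.

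Setting the formula to 10 % gives V = 1.42 and k = 0.42 / 3.6 ≈ 0.12.

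**4. Sensitivity to the event rate.** At 1 event per person-year the simulated error is 7.5 % (k = 0.1), 10.7 % (0.25), 16.4 % (0.5) and 24.9 % (1).

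**5. A test that allows for between-patient variance.** On simulated data of the same kind, a patient-level robust Wald test on the log rate ratio, without small-sample correction, had an error of 5.2 to 6.3 % for k from 0 to 1.5.

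**6. Power once that variance is allowed for.** For a rate ratio of 0.60, expected counts per patient are 3.6 and 2.16. The log rate ratio has variance f / 40 with f = 1/3.6 + 1/2.16 + 2k = 0.741 + 2k, and power = Φ(0.511 / √(f/40) − 1.96). At k = 0.25, f = 1.241, the SE is 0.176, and power = Φ(0.94) ≈ 83 %.

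| k | Power, 40 per arm | Patients per arm for 95 % |
|---|---|---|
| 0 | 96 % | 37 |
| 0.1 | 91.5 % | 47 |
| 0.25 | 83 % | 62 |
| 0.5 | 69 % | 87 |
| 1 | 50 % | 137 |

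The last column already allows for dropout through the 1.8-year mean follow-up.

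**The case against.** **The test's variance is not spelled out.** The article names a comparison of incidence rates but no variance estimator, and a rate ratio with robust or negative binomial variance would also compare incidence rates. A condensed article may leave that to an analysis plan. This weakens the point only in part. The article does fix a group-level estimator and a test of it, and the sample size reproduces with Poisson variance alone.

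**The supporting statements are qualitative.** Every participant must have had a COPD-related hospitalisation or ED presentation in the previous 12 months. Having had recent acute care or not therefore does not vary in this sample, and the Background and Discussion statements do not show how much rates differ among those enrolled. That stands. Heterogeneity remains plausible, because severity ranges from moderate to very severe and the number of prior events can still vary. Stratifying randomisation by centre and FEV1 group balances part of it but leaves variation within strata.

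**Stronger readings that the article does not support.** A reader might infer that false positives are far above 5 % as a matter of fact. They are if k is about 0.25 or more at 2 events per person-year, but at k = 0.05 the error is about 7 %, and no dispersion is given. A reader might also infer that an ED visit ending in admission is counted as two events, which would add to the correlation. The article states no counting rule for this, and the full protocol may, so nothing here rests on it.

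**Conclusion.** The point holds in conditional form. The plan tests pooled group rates with no stated allowance for between-patient variation, and its sample size assumes none. The direction of the error is firm: for any k above 0, a Poisson comparison of these rates rejects too often. The size is not fixed by the article. It runs from about 7 % at k = 0.05 to 36-37 % at k = 1, given gamma-distributed patient rates, 2 events per person-year and 1.8 years' mean follow-up. Modest heterogeneity, k of about 0.12, already doubles the nominal error. The stated 95 % power is also conditional: it belongs to k = 0 and does not carry over to a valid analysis of overdispersed counts. Because this is the primary test, it should be corrected before the data are analysed.

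**What to change.** - In Statistical analysis, replace the Comparison of Incidence Rates with a negative binomial regression of each patient's event count on arm. Use log follow-up time as offset and adjust for the stratification factors, centre and FEV1 group. Poisson regression with patient-level robust variance and a small-sample correction is an acceptable alternative. Report the incidence rate ratio with its confidence interval.
- Use the same model for hospitalisations and ED presentations separately, and keep crude incidence density as a description.
- In Sample size, state the dispersion assumption and give power over a range of k, as in the second table above.

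No new data are needed, since counts and follow-up dates per patient are already collected. The cost is wider confidence intervals and a less favourable stated power. If the sponsor wants to keep 95 % power at a rate ratio of 0.60, more patients are needed: 62 per arm at k = 0.25 and 87 at k = 0.5, against the planned 40.

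### Primary-outcome events stop counting when a patient formally leaves, so analysing everyone as randomised does not remove the influence of dropout as the plan claims

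*Protocol article*

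**What the plan says.** Four statements in the protocol article bear on this.

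- **Statistical analysis, measure and window.** Incidence density is "the number of events in a group divided by the total person-time accumulated during the study in that group". The window is fixed by "All events from the day after randomisation to patient exit/death will be included".
- **Statistical analysis, purpose of intention-to-treat.** All randomised subjects are analysed "to provide unbiased comparisons among groups and avoid the effects of dropout".
- **Adverse events and dropouts.** A dropout is a patient who tells the team that "they do not want to participate any longer to the study and therefore withdraw their consent". Inactivity is handled differently: "Patients who do not participate actively in the intervention will still be included in the study, and analysed according to the intention-to-treat approach".
- **Outcome measures.** Hospitalisations and emergency department (ED) presentations come from "hospitals records (in Australia), regional systems (in Denmark) and national registries (in Norway"). Use of hospital resources is also recorded at follow-up visits, as an addition.

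The Sample size section allows for up to 20 % dropout, spread uniformly over the intervention period.

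**The concern.** Keeping every patient in the randomised arm protects the comparison only for the time during which outcomes are counted. Once events and person-time stop at exit, each arm's rate describes the time before exit. It equals the 2-year rate only if leavers would have gone on having events at the rate observed in their arm.

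The article gives some reason to doubt this, though no proof. The Background names exacerbations and admissions among the obstacles to long-term exercise, and describes earlier admission as a risk factor for readmission. Reasons to stay may also differ by arm. The two treadmill arms keep their equipment at the end, while controls receive standard care. An invitation to continue after an admission, with weekly contact for a month, is described only under the telerehabilitation arm.

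The dropout definition also makes withdrawal of consent follow from no longer wanting to take part. It offers no way to stop visits while allowing record follow-up, although the primary outcome is drawn mainly from records that need no visit. What is at stake is the validity of the primary comparison, not its power.

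**Working it through.** **Inputs from the article.** Control rate 2 events per person-year; rate ratio 0.60, hence 1.2 in the better arm; two-sided alpha 0.05; power 95 %; 65 person-years per group; 40 patients and 80 person-years per arm; up to 20 % uniform dropout; 2 years of follow-up.

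**Assumptions.** Exit occurs at 1 year on average, which is what uniform exit over 2 years implies. Rates after exit are not given in the article, so they are varied below.

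**1. The plan's own figure.** Person-years per group = (1.960 + 1.645)² × (2.0 + 1.2) / (2.0 − 1.2)² = 64.97. The stated 65 reproduces. Allowing for dropout, 65 / 0.8 = 81.25 person-years, close to the 80 enrolled.

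**2. Person-time cut off.** 0.20 × 40 = 8 patients, each losing 1 year on average, gives 8 person-years per arm. That leaves 80 − 8 = 72, a 10 % loss.

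**3. Power.** With Φ[0.8 / √(3.2/T) − 1.96], power is 97.9 % at T = 80, 96.7 % at T = 72 and 94.7 % at T = 64. Precision is not the issue.

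**4. Effect on the rate ratio.** Let f be the share of an arm's 2-year person-time that falls after exit (half the proportion leaving), and m the ratio of the post-exit rate to the observed rate. Then

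full rate = observed rate × [1 + f(m − 1)],

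and, with a censored ratio of 0.60,

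full ratio = 0.60 × [1 + f_T(m_T − 1)] / [1 + f_C(m_C − 1)],

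where T is telerehabilitation and C is control.

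| Assumed pattern | Leaving, C / T | Calculation | Full 2-year ratio |
|---|---|---|---|
| Exit unrelated to rate | any | m = 1 in both | 0.60 |
| Rate doubles after exit, equal exits | 20 % / 20 % | 0.60 × 1.10 / 1.10 | 0.60 |
| Telerehabilitation leavers revert to control rate (m_T = 2.0/1.2) | 20 % / 20 % | 0.60 × 1.067 | 0.64 |
| Same reversion | 10 % / 30 % | 0.60 × 1.10 | 0.66 |
| Rate doubles after exit | 10 % / 30 % | 0.60 × 1.15 / 1.05 | 0.66 |
| Rate doubles after exit | 30 % / 10 % | 0.60 × 1.05 / 1.15 | 0.55 |

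With neither arm above 20 %, doubling gives 0.60 × 1.10 / 1.05 = 0.63 (10 % / 20 %) or 0.60 × 1.05 / 1.10 = 0.57 (20 % / 10 %).

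The range 0.55 to 0.66 is not a bound. Combining reversion and doubling in the 10 % / 30 % case (m_T = 4.0/1.2) gives 0.60 × 1.35 / 1.05 = 0.77.

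**5. Against sampling error.** At 72 person-years the expected events are 144 and 86.4, so the Poisson standard error of the log ratio is √(1/144 + 1/86.4) = 0.136. A shift from 0.60 to 0.657 (the doubling case at 10 % / 30 %, before rounding) is ln(1.095) = 0.091, about two-thirds of one standard error.

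**The case against.** The strongest reply is that the article already protects the group most likely to cause trouble. Someone who deteriorates and stops exercising is not an exit and is still counted. A reader might infer that all patients who give up training because they worsen are lost. The dropout section says otherwise, and this part of the objection stands in full. What remains is formal leavers, for whom the Sample size section makes its dropout allowance.

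A second reply is that stopping event collection when consent is withdrawn follows from the definition. A reader might infer that post-exit records are freely available to the trial. The article shows only that the sources do not depend on visits. It does not say that they may be used after withdrawal. This stands too, and it is why leavers have to be asked.

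A third reply is that graded withdrawal and sensitivity analyses often sit in a consent form or analysis plan that is not shown. Their absence is therefore not the point. The point is that the article states a censoring rule, a definition that merges two decisions, and a claim that the rule does not support.

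A fourth reply concerns size. If one arm alone lost 8 person-years at a doubled rate, its true rate would be (144 + 32) / 80 = 2.2 against a recorded 2.0. A reader might take that 10 % as the expected distortion. Nothing in the article supports either the doubling or its restriction to one arm, and equal exits with equal doubling cancel.

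**Conclusion.** The claim that intention-to-treat removes the influence of dropout is too strong for a rate truncated at exit. It holds for the censored patients only if leaving is unrelated to admission risk, which the article does not state. The Sample size section itself expects dropout to remove person-time.

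The exposure is limited to formal leavers: up to 20 % of patients and about 8 of 80 person-years per arm. Under the assumed patterns, a censored ratio of 0.60 corresponds to a full 2-year ratio of roughly 0.55 to 0.66. The shift may favour telerehabilitation or count against it. These figures rest on assumed exit proportions and post-exit rates. They show that bias is possible, not that it will occur. No sample-size figure is wrong on this account.

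The point is worth acting on because the remedy is cheap and replaces a stated censoring rule with one less open to bias.

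**What to change.** 1. In Adverse events and dropouts, separate stopping study participation from withdrawing permission to use records, and ask each leaver about the second.
2. For leavers who permit it, count hospitalisations, ED presentations and deaths in records to 2 years after randomisation (or to death), with the matching person-time, in the primary intention-to-treat analysis.
3. Censor at exit only those who refuse, and define exit accordingly in Statistical analysis.
4. Report the analysis to exit as a sensitivity analysis.
5. Replace the dropout claim with the assumption that censoring is non-informative for those still censored.

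The cost is a short consent amendment in three jurisdictions and a few extra record extractions. Some leavers will still refuse, so the assumption is narrowed rather than removed. The Trial status section reports that recruitment was continuing, so the change could still reach later leavers.
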